*** Amendments to the original plan have been marked with red writing.**

1. **Background**

SYSDIET (Systems biology in controlled dietary interventions and cohort studies) is one of the three centres in the NCoE Food, Nutrition and Health, 2007-2011. It consists of 12 partners from five Nordic countries working on multidisciplinary fields of science related to nutritional biology. The main objective of SYSDIET is to reveal mechanisms by which Nordic foods and diets could be modified to promote health and prevent insulin resistance, type 2 diabetes and cardiovascular diseases, all of which being connected to metabolic syndrome. Furthermore, the aim is to build up a Nordic platform for cohort studies and carefully conducted multi-centre dietary intervention studies, where novel nutritional systems biology tools can be applied besides human studies also in animal and cell culture studies.

In order to achieve the main objective a Nordic multi-centre randomized controlled human intervention study is being conducted in 2009-2010 in 6-8 centres of SYSDIET consortium. In the following, a condensed study plan is presented for this dietary intervention study aiming primarily at finding out the effects of healthy Nordic food in persons with features of metabolic syndrome. This study plan is based on the discussion of the SYSDIET consortium in Oslo, April, 10-11, 2008.

Health of the Nordic populations has substantially improved during the last 30 years. This is due e.g. to marked decline in cardiovascular morbidity and mortality. However, during the last 10-20 years increasing obesity and sedentary lifestyle have resulted in an increase of metabolic syndrome and type 2 diabetes. This concerns not only middle-aged people but also children and adolescents. The prevalence of metabolic syndrome is 15 to 36 % in different study populations among middle-aged and elderly people, but figures may vary among different nations. It has been suggested that the epidemic of obesity/metabolic syndrome/type 2 diabetes may arrest the beneficial development of a nation’s health achieved within the last decades in Nordic countries. Therefore, we decided in the SYSDIET consortium to focus our research interest on metabolic syndrome and its consequences and especially on the prevention and treatment of metabolic syndrome by changes diet according to Nordic recommendations from 2004. Furthermore, in this consortium we aim to find out early biomarkers, which are related to the development of metabolic syndrome. These biomarkers could be originated from our diet or they may be “new” metabolites linked to the risk of metabolic syndrome. Along with this line, systems biology approaches are being applied in our studies on diet and metabolic syndrome.

Metabolic syndrome can be described as clustering of risk factors, which links it to an increased risk of type 2 diabetes and atherosclerotic vascular diseases. Several criteria have been created as to definition of metabolic syndrome. Recently central obesity has been considered as a new key feature, due to its simplicity to measure. The International Diabetes federation criteria for metabolic syndrome have been listed in Table 1.

The main risk factors of metabolic syndrome and type 2 diabetes are obesity, in particular central obesity, and sedentary lifestyle. In addition, overall quality of diet, diet rich in fat and saturated fatty acids, high glycaemic index carbohydrate diet as well as diet low in dietary fibre have been shown to associate with the risk of these conditions. In some epidemiological studies fish intake has been shown to be protective in terms of the risk of diabetes, but short-term human intervention trials have not confirmed the relation between glucose and insulin metabolism and fish or omega-3-fatty acid intake. Omega-3-fatty acids have many other beneficial effects, which could be of interest regarding clinical features of metabolic syndrome and the risk of atherosclerotic vascular diseases. Interestingly, fish protein is recently suggested to have lowering effects on blood pressure, but this finding should be confirmed by further studies.

**Table 1.** Criteria of the metabolic syndrome by International Diabetes Federation.

| **Primary Criterion:** |  |
| --- | --- |
| Central Obesity | Waist circumference - ethnicity specific: men >94 cm, women: >80 cm |
|  |  |
| **Plus any two:** |  |
| Raised triglycerides | >150 mg/dL (1.7 mmol/L) |
|  | Specific treatment for this lipid abnormality |
|  |  |
| Reduced HDL-cholesterol | <40 mg/dL (1.03 mmol/L) in men  <50 mg/dL (1.29 mmol/L) in women |
|  | Specific treatment for this lipid abnormality |
|  |  |
| Raised blood pressure | Systolic [figure not shown]130 mm Hg  Diastolic [figure not shown]85 mm Hg |
|  | Treatment of previously diagnosed hypertension |
|  |  |
| Raised fasting plasma glucose | Fasting plasma glucose [figure not shown]100 mg/dL (5.6 mmol/L)  Previously diagnosed type 2 diabetes |

(Alberti KGMM et al. The metabolic syndrome - a new worldwide definition, Lancet 2005)

Whole grain cereal products, fruit, berries and vegetables have been shown to be protective against many chronic diseases. The consumption of whole grain cereal products, fruit, berries and vegetables has been promoted by various recommendations including Nordic recommendations from 2004 (Nordic Nutrition Recommendations 2004, 4th edition, NORD 2004:13). Mediterranean diet has gained a lot of interest due to its health benefits. The key dietary items in this health promoting diet are fruit, vegetables, fish and olive oil. Both epidemiological and some dietary intervention studies have shown that Mediterranean diet may protect against cardiovascular diseases. More specifically, olive oil, which is rich in monounsaturated fatty acids, is beneficial also in terms of lipid and glucose metabolism.

The aim of the Nordic Dietary recommendations is to promote public health integrating nutrition and physical activity. These recommendations are based on solid scientific evidence with regard to prevent chronic diseases, e.g. atherosclerotic vascular diseases, obesity, metabolic syndrome and type 2 diabetes. In principle, the composition of Nordic healthy food is in line with other dietary recommendations. They emphasize energy balance, restriction of the intake of saturated fats, moderate intake of unsaturated fats, increased use of dietary fibre, fruit, berries, vegetables and whole grain cereal products, and use of low fat dairy products. Furthermore, salt intake should be reduced in long-term. As for fish intake, regular consumption of fish, both fatty and lean varieties, is recommended. This means two fish meals per week.

Based on recent findings e.g. from Finland, persons with metabolic syndrome have poorer quality of diet as compared to people without this condition. Thus, dietary patterns are differentiating people in relation to their health status. Several long-term intervention trials, e.g. the Finnish Diabetes Prevention Study, show that weight reduction, moderate increase in physical activity and beneficial dietary changes according to current recommendations result in the decrease in the risk of type 2 diabetes and metabolic syndrome. However, it has remained an open question as for what is the role of changes in the quality of diet without simultaneous weight loss and increased physical activity. More importantly, there are no studies available testing whether a healthy Nordic diet could reduce the main biochemical and physiologic abnormalities of metabolic syndrome. Furthermore, Nordic food includes many other ingredients which may be beneficial in the prevention of chronic diseases. In particular phytochemicals are gaining increasing interest due to their potential health effects. Therefore, more information is urgently needed in order to explore the health potential of healthy Nordic foods in promotion of health and prevention and treatment of chronic diseases, especially metabolic syndrome.

1. **Aims of the study**

Having this background, the aim of the SYSDIET consortium is to carry out a controlled, randomized dietary intervention study in persons with features of metabolic syndrome to find out the effects of a healthy Nordic food on major abnormalities in metabolic syndrome.

**Specific objectives:**

1. To find out to what extent a Nordic healthy food could improve insulin sensitivity and other metabolic/physiological abnormalities in persons with features of metabolic syndrome
2. To identify new early markers for insulin resistance/metabolic syndrome in serum and urine
3. To study the effects of the healthy Nordic food on gene expression in adipose (AT) tissue and peripheral blood mononuclear cells (PBMCs)
4. To study the effects of the healthy Nordic food on lipid and metabolite profiles (metabolomics)
5. To examine how healthy Nordic food may effect on gut flora
6. To build up Nordic consortium (platform) to carry out controlled dietary intervention studies to make Nordic countries more competitive in food science and human nutrition studies

When it comes to metabolic syndrome several outcome measures are to be considered. Nevertheless, insulin resistance is a characteristic feature in this condition. Therefore, the main outcome measures will be insulin resistance index and insulin secretion index both of which are based on oral glucose tolerance test (OGTT) with 0, 30 min, and 120 min glucose, insulin and triglyceride values.

1. **Study design**

The study design is described in the Figure 1. Recruited persons will start the study by following their conventional diet for one month as a run-in period. After that subjects will be randomly assigned into Experimental- (Exp) or Control- diet-group for 6 months. They will visit the study clinic at 2, 4, 8, 12, 16, 20 and 24 weeks. At each visit body weight and BP will be measured. The major visits are in the beginning (0 week) and at 12 and 24 weeks (end of the study), and will be done after 12 hour fasting. Subjects should drink 2.5 dl water both in the evening and in the morning during the fasting period before the study visits. Staff in all study centers will be trained to perform the measurements and quality management protocol. Standard operational procedures will be followed in all measurements.

**The original protocol was changed after the discussion with the Food, Nutrition and Health –program Scientific Advisory Board and Steering Group members due the following reasons:**

**1. A shorter period of intervention will give the same information as that obtained from 24 weeks trial.**

**2. Total costs will be lower and recruitment of subjects easier to carry out.**

**3. Analyses will be started earlier in September 2010.**

**Therefore, it was decided to shorten the intervention to 18 weeks in Århus, Uppsala, Reykjavik and Oulu. This means that the last visit will happen at week 18, but otherwise the visits to the study centres will happen according to original study plan. In the analyses of the major outcome measures no changes are allowed (see below).**

Because physical activity, alcohol intake, smoking, body weight and drugs are known to affect the characteristics of metabolic syndrome, the study persons are advised to keep physical activity constant, and not to change their smoking and drinking habits or drug treatment during the study.

Planning phase of the study was started in 2008 and the trial will be carried out in 2009-2010.

- 1. **Screening**

At the first visit 1 month before the study a screening examination will be carried out. The visit includes medical history, clinical examination, body weight, height, waist circumference, blood pressure, blood count, fasting plasma glucose and fasting serum creatinine, tyreotropin stimulating hormone (TSH), gamma-GT, AFOS, ALAT, triglycerides, total and HDL-cholesterol. Electrocardiogram (ECG) will also be measured based on medical history. Fasting plasma glucose value should be <7.0 mmol/l. If the 2-h glucose value > 11.0 mmol/l will be found in the OGTT in the beginning of the intervention, subject’s eligibility to continue in the study will be evaluated by a study physician.

[figure not shown]

**Figure 2.** Study design in the diet intervention. PBMC= peripheral mononuclear cells.

* If the final visit will be done on the study week 18, the study visit on the week 16 is optional.

** Study visit at week 20 will be made if the intervention is planned to last 24 weeks, as originally decided.

**In two centres, Lund and Kuopio, the original study plan will be followed, whereas in all other centres the final study visit will happen at week 18. In statistical analyses regarding the major outcome measures this change is possible to take into account. It is expected that no major changes in variables of interest will any more happen between the weeks 18 and 24. The changes made in the study protocol should be informed appropriately. Of note, the trial has also been registered as a clinical trial (NCT00992641).**

- 1. **Study subjects**

Altogether **180 - 200 subjects** aged 30 to 65 years will be recruited from 6 centers (20-40 subjects/center) of the SYSDIET cohort. The inclusion criteria are listed in Table 2. The main inclusion criterion is BMI 27-38 kg/m2. The subjects should also have at least two other IDF criteria for metabolic syndrome listed in Table 1, except diagnosed type 2 diabetes. Persons will be screened mainly through advertising in newspapers, but also from previous clinical or epidemiological trials. The aim is to have male subjects at least 1/3 of the whole study group. Moreover, since the IDF criteria concern the Caucasian population, only Caucasians are included in the study. The use of anti-hypertensives and lipid lowering drugs should not be discontinued during the intervention. Based on the recent experiences from clinical trials and new power calculations 80-90 persons in each group will be expected to give appropriate power for the study (alfa level < 0.05, beta level 0.80).

**Table 2**. Inclusion criteria.

| Variable | Inclusion |
| --- | --- |
| Age | 30-65 years |
| BMI | 27-38 kg/m2 |
|  |  |
|  | + two other IDF criteria for metabolic syndrome (Table 1, except diagnosed type 2 diabetes) |
| Medication | Anti-hypertensives and lipid-lowering medication are allowed |

**3.3 Exclusion criteria**

The exclusion criteria are summarized in Table 3. The main exclusion criteria include any chronic disease and condition, which may hamper to follow dietary intervention protocol, poor compliance, chronic liver, thyroid and kidney diseases, alcohol abuse (> 40 g/d), known diabetes, fasting plasma glucose >7.0 mmol/l and BMI above 38 kg/m2.

Other exclusion criteria are a recent myocardial infarction (< 6 month), corticosteroid therapy, psychiatric disorders which need drug treatment, cancer under treatment, coeliac disease, allergies to cereals or fish and other serious and extensive food allergies. Exceptional diets (such as Atkin's or vegan diet) before the study are also an exclusion criterion as well as binge eating. Binge eating will be screened by using a validated questionnaire (Spitzer et al. 1993).

Inhaled corticosteroids are permitted. Fish and vegetable oil supplements should be discontinued at least 4 weeks before the beginning of the intervention (in the beginning of the run-in period). Moreover, the use of stanol or sterol esters should be discontinued in the beginning of the run-in period. Unwillingness to discontinue the use of these supplements and/or products is an additional exclusion criterion.

**Table 3**. Exclusion criteria

| Variable | Exclusion | Possibility for inclusion |
| --- | --- | --- |
| Fasting plasma glucose | > 7.0 mmol/l |  |
| Fasting plasma triglycerides | > 3.0 mmol/l |  |
| Fasting plasma total cholesterol | > 6.5 mmol/l |  |
| Blood pressure | > 160/100 mmHg | Should be stabilized with medication, after which the intervention can be started. |
| Preceding weight change | 5% or active weight loss during preceding 6 months |  |
| Chronic disease or condition | Any that may hamper the successful participation of the intervention (see background information form) |  |
|  | Liver disease |  |
|  | Kidney disease |  |
|  | Diabetes (both type 1 and type 2) |  |
| Thyroid disease | Newly found, unstabilized disease | Stabilized with medication |
| Myocardial infarction | Within previous 6 months |  |
|  |  |  |
|  |  |  |
|  |  |  |
| Alcohol abuse | > 40 g/day |  |
| Corticosteroid therapy | Oral medication | Inhaled, cream, lotion |
| Psychiatric disorders | Severe, with medication | ‘Mood’ medication |
| Cancer | Under treatment | Cured cancer allowed |
| Coeliac disease | Gluten free diet |  |
| Exceptional diets | Atkin’s, vegan, allergies to fish or cereals, other extensive allergies |  |
| Binge eating | Score of the BED in the QEWP questionniare |  |
| Fish and vegetable oil supplements | Unwillingness to discontinue the use of the supplements |  |
| Stanol and sterol esters | Unwillingness to discontinue the use of stanol/sterol containing products |  |

**3.3.1 Exclusion criteria during the intervention**

The participation of an uncompliant subject who repeatedly does not follow the instructions and does not consume the study products should be discontinued. The allowed weight change during the study is ± 2-3 %.

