**3.4 Study diets**

The principles of the Exp-diet are summarized in Tables 4 and 5. Diet will be isocaloric based on the evaluation of the habitual diet made by a dietitian or a clinical nutritionist. The energy intake level of the diet will be planned based on the individual energy intake (calculated from food record) or estimated requirement. Mean total fat intake of 30-35 E% is divided into saturated fat intake ≤ 10 E% and mono- and polyunsaturated fat intake minimum 2/3 of total fat intake. Mean carbohydrate intake is 45-52 E% with the main emphasis to increase the use of whole grain cereal products of typical Nordic varieties such as rye, barley and oats. Intake of fruit, vegetables and berries should be ≥500 g. The aim for fiber intake is >35 g/d. Fish should be included in the diet >3 times (100-150 g /portion) per week of which 2 meals/week should be fatty fish. By choosing foods with low salt content the aim is to decrease salt intake to <7 g/d.

The food composition of the C-diet varies among Nordic countries, although the nutrient intake is close to each other in each country. The calculations of the dietary composition and mean nutrient intake in the C-diet are based on the mean intake figures in the five Nordic countries. Overall diet should be isocaloric and based on the evaluation of the habitual diet made by a dietitian or a clinical nutritionist. Differing from the Exp-diet, the mean intake of the total fat is about 35 E% divided into the intake of saturated fatty acids 15 E%, monounsaturated fatty acids 15 E% and polyunsaturated fatty acids 5 E%. Dietary fiber intake will be the typical Nordic intake of 15-20 g/d with habitual low consumption of fruits, vegetables and berries. The mean salt intake should be 10 g/day at its highest (Tables 4 and 5).

**Table 4**. Mean nutrient composition of the study diets*.

| **Nutrient** | **Experimental diet** | **Control diet** |
| --- | --- | --- |
| Carbohydrate (E%) | 45-52 | 45-47 |
| Sucrose (E%) | ≤ 10, max. 50 g/day | no restrictions |
| Fibre (g) | ≥ 35 g or 4g/MJ | 15-20 |
| Protein (E%) | 18-20 | 18-20 |
| Fat (E%) | 30-35 | 35 |
| Saturated (E%) | < 10 | 15 |
| Monounsaturated (E%) | minimum 2/3 of total fat intake | 15 |
| Polyunsaturated (E%) |  | 5 |
| Salt (g) | 6 g for women, 7g for men | ≤ 10 |

*Control diet is based on habitual diets in five Nordic countries with some modifications. Experimental diet is based on the Nordic recommendations.

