| **Fish** | **≥ 3 meals /week:**  **2 fatty fish (min. 4-5 % of fat) meals + 1 low fat fish meal**   - e.g. salmon, rainbow trout, Baltic herring, whitefish, vendace, pike, haddock, halibut, trout, herring, mackerel, cod, saithe, plaice, mackerel, sardines, brisling - Norway: herring and mackerel also available as spreads - Iceland: cod liver oil discontinued at least 4 weeks before the beginning of the intervention; replacement by pure D-vitamin supplements | **≤ 1 meal / week** |
| **Meat** | **Preferably white meat, poultry**  **Low fat choices**  **Game**   - e.g. poultry, lamb (lean products, **≤** 10 % of fat), game, pig (lean products, **≤** 10 %), beef (lean products, **≤** 10 %) | **No limitations**   - same, but less lean |
| **Soft drinks**  **Fruit and berry juices** | **Sugar-containing soft drinks should be avoided.**   - The use of artificially sweetened drinks should be limited to 1-2 glasses per day.   **≤ 1 glass (1.5 dl)/day**   - Finland: "National drink recommendation" allows 1-2 glasses of juices per day along with a meal and in the study diet sucrose limitation (max 50g/day) allows this, thus we see that 1 glass/day should be ok | **No limitations**  **No limitations** |

1. **Measurements**

The attached table (clinical, anthropometric and biochemical measurements) summarizes the main measurements that will be performed during the study. The methodology of analyses of the blood samples will be centralized concerning the non-rutine measurements and is based on the expertise of the partner center. These samples will, thus, be sent to these centers. Other measurements and analyses will be done locally in the performing centers according to the standard operational procedures to be accepted by the Management Group of the NCoE SYSDIET.

**Appendix 1 shows the participating centres and their responsibility regarding the intervention trial and analyses, which will be started in September 2010.**

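### Section 3.3.1 ends the participation of randomised non-compliers without a threshold or any outcome follow-up, so unequal removal between the diets may bias the OGTT-based main outcomes.

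*Protocol*

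**What the plan says.** Under a heading about exclusion during the intervention, section 3.3.1 states: "The participation of an uncompliant subject who repeatedly does not follow the instructions and does not consume the study products should be discontinued". The same section adds a limit on body weight, "The allowed weight change during the study is ± 2-3" per cent, without saying what follows if a subject exceeds it.

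The rule operates after allocation. Following the one-month run-in, the Study design section states: "After that subjects will be randomly assigned into Experimental- (Exp) or Control- diet-group for 6 months". It also says: "The major visits are in the beginning (0 week) and at 12 and 24 weeks (end of the study". The amended text moves the last visit to week 18 in four centres. On endpoints, the text after the specific objectives states that "the main outcome measures will be insulin resistance index and insulin secretion index both of which are based on oral glucose tolerance test (OGTT".

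The two diets are set out in section 3.4 and Tables 4 and 5. The experimental diet asks for at least 500 g of fruit, vegetables and berries, at least 6 slices of high-fibre bread a day, and at least three fish meals a week ("2 fatty fish (min. 4-5 % of fat) meals + 1 low fat fish meal"), with limits on sucrose, salt and saturated fat. The Table 4 footnote describes the comparator: "Control diet is based on habitual diets in five Nordic countries with some modifications".

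The protocol gives no compliance threshold, no assessor, no expected withdrawal rate for either arm, and no statement that a discontinued subject is still measured.

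**The concern.** What section 3.3.1 ends is participation, not only the diet. A subject discontinued before week 18 or 24 has no end-of-study OGTT unless someone arranges one, and the protocol does not ask for that. Both main outcomes are computed from that test.

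The subjects lost this way are selected by their behaviour after randomisation. If more of them are lost from one arm, and if they would have had worse indices than those who stay, the subjects who remain are no longer comparable between arms. Part of any observed difference would then reflect who was kept and not what they ate.

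The fault lies in the conduct rule and is not something left to the statistical analysis plan. A plan can declare that all randomised subjects are analysed, but it would have to impute the missing indices under an assumption that the trial data cannot test.

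**Working it through.** **The plan's own figure.** Section 3.2 gives 80-90 subjects per group, with alpha 0.05 and what it calls a beta level of 0.80 (read here as power). No effect size or SD is stated, so the number cannot be reproduced. It can be turned round. With a two-sided test and equal arms, the detectable standardised difference is d = (1.960 + 0.842) × √(2/n):

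- n = 80: 2.802 × √(2/80) = 0.443 SD
- n = 90: 2.802 × √(2/90) = 0.418 SD

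This is the yardstick for the bias below.

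**Bias from removal.** Suppose the diet has no effect and the SD is 1. Let fE and fC be the fractions removed on the experimental and control diets, and let removed subjects be D SD worse than retained subjects in each arm. The retained mean in an arm then exceeds that arm's full mean by f × D, so:

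- bias = (fE − fC) × D
- SE = √[1/(n(1 − fE)) + 1/(n(1 − fC))]
- type I error = P(|Z + bias/SE| > 1.960)

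**Inputs.** n = 85 per arm is the middle of the protocol's 80-90. The values of fE, fC and D are assumptions, because the protocol gives none of them. D is taken as 0.3-0.5 SD.

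| fE | fC | D (SD) | Bias (SD) | SE | Type I error |
|---|---|---|---|---|---|
| 10% | 10% | 0.5 | 0 | 0.162 | 5.0% |
| 10% | 5% | 0.3 | 0.015 | 0.160 | 5.1% |
| 15% | 5% | 0.3 | 0.030 | 0.162 | 5.4% |
| 20% | 5% | 0.5 | 0.075 | 0.165 | 7.4% |
| 20% | 0% | 0.5 | 0.100 | 0.163 | 9.4% |
| 30% | 5% | 0.5 | 0.125 | 0.171 | 11.3% |
| 30% | 0% | 0.5 | 0.150 | 0.169 | 14.4% |

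The last row in full: bias = 0.30 × 0.5 = 0.150; SE = √(1/59.5 + 1/85) = 0.169; bias/SE = 0.887; type I error = 14.4%.

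Over the range 15-30% against 0-5% and D of 0.3-0.5, the bias runs from 0.03 to 0.15 SD. Against the detectable difference, that is from 0.03/0.443 = 7% to 0.15/0.418 = 36%. The first two rows lie outside that range and show how quickly the problem fades when removal is similar in the two arms.

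**The case against.** A reader might infer that the trial will compare compliers on a demanding diet with nearly everyone on control. The documents do not support that.

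- The rule names no arm and so covers both.
- As worded it needs two conditions together: instructions repeatedly not followed, and study products not consumed. That describes gross non-adherence, not a missed portion of fruit.
- The control diet has real restrictions in Table 5: refined cereals that are at least 90% wheat, no rye sourdough, butter or milk-fat spread, no bilberries, few other berries, and at most one fish meal a week. Someone who habitually eats rye bread and fish would have to change.
- Sections 5.2 and 5.3 make the experimental diet easier to follow: fish costs are reimbursed, other key foods are supplied, and advice is individual.

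It is also tempting to say that discontinued subjects are dropped from the analysis. The protocol does not say that collected data are discarded or that an exit visit is refused. Week 12 is a major visit, so a subject stopped later may have some on-diet data, although the text shown does not settle whether an OGTT is done then. The poor-compliance item in section 3.3 belongs to the general exclusion list and is not evidence about the on-study rule.

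Finally, the magnitude rests on assumed rates and an assumed prognostic gap. Adjustment for the week-0 OGTT would make the relevant gap the baseline-adjusted one, which may be smaller than 0.3-0.5 SD.

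All of this stands as a limit on how strongly the point can be put. It does not remove the core: participation ends because of behaviour after randomisation, no threshold makes the decision uniform across centres, and no outcome measurement is provided for afterwards.

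**Conclusion.** The point holds as a design defect with a risk of bias, not as a demonstrated bias. Followed as written, section 3.3.1 can remove randomised subjects from both main outcomes in a way that later analysis cannot repair.

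Greater loss in the experimental arm is a reasonable expectation from the two diet prescriptions, and the likely direction then favours the experimental diet. This needs two things that the protocol does not quantify: unequal removal, and worse outcomes in those removed. Under the assumed ranges the effect goes from negligible (0.03 SD, type I error 5.4%) to serious (0.15 SD, about 14%). With equal removal and equal prognostic gaps there is no bias, only fewer subjects.

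The stated sample size is neither confirmed nor refuted by this check.

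**What to change.** Reword section 3.3.1 so that ending the study diet for non-compliance does not end follow-up:

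- Invite such subjects to the remaining major visits, including the final OGTT at week 18 or 24.
- State how non-compliance is established, so that centres apply the rule alike, and record the reason for each discontinuation by arm.
- Analyse these subjects in their assigned group, and use compliance only to define a secondary per-protocol analysis. This part may sit in the statistical analysis plan; the follow-up must be in the protocol.
- State what the weight limit in the same section leads to, and whether outcome measurement continues when it is exceeded.

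The wording change is a sentence or two, and the visits are already scheduled. The costs are the effort of bringing non-compliers back and a somewhat diluted estimate. As an illustration, take 90 per arm, a true effect of 0.418 SD in compliers, and 10% of the experimental arm gaining nothing. The analysed effect is 0.418 × 0.9 = 0.376 SD and power is 71%. If those 10% were removed and did not differ in prognosis, power would be 78%. The lower figure is the price of a comparison that randomisation still protects.
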